## Abstract

**Background:**

Approximately 30 to 50% of women are unable to correctly perform pelvic floor muscle (PFM) contractions. For women to benefit from a pelvic floor muscle training (PFMT) programme for stress urinary incontinence (SUI), the awareness phase of PFMT cannot be omitted. The purpose of this study is to evaluate whether vaginal palpation together with verbal instructions about PFMs and body awareness techniques helps women with SUI learn how to correctly contract the PFMs and improve their functions.

**Methods:**

This single-centre, double-blind randomized controlled trial with two intervention groups was designed following the standard protocol items for randomized interventional trials (SPIRIT). The results will be reported in a manner consistent with the Consolidated Standards of Reporting Trials (CONSORT) guidelines. Patients with SUI (*n* = 172) will be recruited. The experimental group will receive verbal instructions about PFM function and body awareness techniques together with vaginal palpation; the control group will receive similar protocol without vaginal palpation. The primary outcome includes the number of fast-twitch muscle fibres assessed by vaginal palpation and visual observation. Secondary outcomes include power and muscular endurance that will be assessed by visual observation and vaginal palpation (Oxford scale), the use of accessory muscles during the voluntary contraction of PFMs, and the self-efficacy and the expectations for the results using the self-efficacy scale of pelvic floor exercises.

**Discussion:**

This study will determine whether vaginal palpation can help women with SUI to correctly perform PFM contractions and improve their functions.

**Trial registration:**

ClinicalTrials.gov NCT 03325543. Registered on 30 November 2017. Study protocol version 1; 30 November 2020. Prospectively registered.

## Introduction

Stress urinary incontinence (SUI) is defined as an involuntary loss of urine during effortful manoeuvres, such as coughing or sneezing [1]. Pelvic floor muscle training (PFMT) is a conservative and first-line treatment for women with SUI [2] that can be included in both outpatient and home care regimens. The success rate of the outpatient regimen ranges from 60 to 75% [3, 4], and that of the home regimen ranges from 9 to 17% [3, 5]. However, in practice, approximately 30 to 50% of women are unable to correctly perform perineal muscle contractions. Some factors may contribute to this finding, such as the location of the pelvic floor muscles (PFMs), their small size, and the general lack of knowledge on the pelvic and perineal regions and their functions. In addition, women usually initially contract their gluteal, hip adductor, or abdominal muscles rather than their levator anus muscle when asked to contract their PFMs [6–9]. For women to benefit from a PFMT programme for the treatment of SUI, the awareness phase of PFMT cannot be omitted; all relevant previous studies have suggested that pelvic floor exercises improve the recruitment capacity of the musculature and its tone and individuals’ reflex coordination during effortful activities [7, 10].

The overall objective of this study is to evaluate whether vaginal palpation together with verbal instructions about the anatomy and function of the PFMs and the use of body awareness techniques helps women with SUI learn how to correctly contract the PFMs and improve their function.

## Objectives and hypothesis

The specific objectives are to compare the experimental group (verbal instructions + body awareness techniques + vaginal palpation) and the control group (verbal instructions + body awareness techniques) with regard to the following factors:
The number of fast-twitch muscle fibres, as determined by the number of effective contractions (fast contractions with maximal force lasting 1 s each) out of ten contractions performed [11], before and immediately after the intervention;PFM function (voluntary contraction of the PFMs) and muscular endurance (duration of the muscular contractions in seconds), as measured by the Oxford scale [11], before and immediately after the intervention;The occurrence of associated contractions of the abdominal, gluteal, and adductor muscles during the voluntary contraction of the PFMs before and immediately after the intervention; andSelf-efficacy, before and immediately after the intervention, as measured by the self-efficacy scale for the practice of pelvic floor exercises [12].

The hypothesis of the present study is that the experimental group (verbal instructions + body awareness techniques + vaginal palpation) will have significantly more effective fast phasic fibres (contractions assessed by digital palpation) than will the control group after undergoing the interventions, as determined by the primary outcome.

## Methods

### Design

The present study is a single-centre, double-blind (investigators and outcome assessors) randomized controlled trial with two physiotherapy intervention groups. The study was designed following the Standard Protocol Items: Recommendations for Interventional Trials, and the results will be reported in a manner consistent with the consolidated standards of reporting trials (CONSORT) guidelines [13].

### Research site

The research will be conducted in the Urogynaecology and Reconstructive Pelvic Surgery Sector at the Federal University of Sao Paulo in Brazil. The participants will complete one training session per week for 1 month (four sessions) in the urogynaecology clinic. The physiotherapist (PT) will supervise all of the participants during their weekly visits and monitor each subject’s technique, dose (quantity of exercise), and appropriate progression of the exercise programme according to the body and perineal awareness protocol proposed by this study. In addition to the outpatient sessions, the participants will perform the exercises at home.

### Recruitment procedures

Consecutively, included patients with urinary symptoms will be evaluated by a urogynaecologist, who will perform a clinical examination (patient history and physical exam, including a stress cough test) and pad test. Patients with SUI and/or mixed urinary incontinence with predominant SUI symptoms and ≥ 2 g leakage on the pad test will be considered candidates for conservative treatment. The specific type of incontinence will be diagnosed on the basis of clinical parameters, the pad test results [1, 14], and the patients’ reports of which condition bothers them the most (stress urinary or urge incontinence). The patients will then be referred to a PT for the consideration of conservative treatment.

### Participants

The participants will be instructed about the study and asked to provide written informed consent (Additional file 1), which will be obtained by the PT investigator ([name]). The PT ([name]) specialist in rehabilitation of the PFMs will evaluate the patients’ PFM function using vaginal palpation and visually observing the movement of the perineum during contractions. We will include women who have SUI symptoms; have ≥ 2 g of leakage, as measured by a 1-h pad test; have not previously undergone physiotherapy for pelvic floor dysfunction; and have at least grade 1 muscle strength (flicker), as assessed by the two-finger assessment and rated according to the Oxford scale [11]. Patients will not be included if they are younger than 18 years old; have chronic degenerative diseases; have pelvic organ prolapse more severe than stage I, as determined by the POP-Q; have neurologic or psychiatric diseases; have a history of pelvic floor surgeries; or have any intolerance or discomfort in response to the PFM examination.

### Randomization procedures

The participants will be randomly assigned to either the experimental group or the control group. The allocation sequence will be generated by a research assistant ([name]) using a computer-generated random number table with a group ratio of 1:1 and will be concealed in sequentially numbered, sealed, and opaque envelopes. The envelopes will be kept in a closed locker at the centre to which only the research assistant will have access. The envelopes will be given to the PT ([name]) immediately prior to the first outpatient session.

### Blinding

The researchers involved in data acquisition [outcome measures ([name])], data analysis, and/or statistical analysis (professionals without knowledge of the results) will be blinded to the group allocation. The PT responsible for the physiotherapeutic treatment ([name]) will not be blinded to the allocation of the patients in the groups and, therefore, will not be involved in data acquisition, data analysis, and/or statistical analysis. The participants will not be blinded to the group they are assigned to since the control group will not undergo vaginal palpation as part of the perineal awareness programme. The epidemiological, clinical, allocation, randomization, and outcome data from the study will be stored by the principal investigator in a virtual database to which only he will have access. At the end of the study, the results will be made available to researchers who did not have contact with the participants as well as to statisticians blinded to the groups, and these researchers and statisticians will perform the data analysis.

### Interventions

Both therapy programmes (experimental group, control group) are based on training procedures for motor learning (understanding; searching; learning; control) [7]. The training programme will last for 4 weeks and will include 4 personal physiotherapy consultations. The main difference between the programmes is the applied technique (experimental group: vaginal palpation; control group: verbal instructions). More details on the intervention (therapy plan of the experimental group and control group) are included in Additional file 2. Patients will be encouraged to carry out treatment completely, through text messages (sent weekly by cell phone) that will encourage them to improve their PFM function through their personal effort and will reduce the rate to dropouts. In the event that dropouts of more than 15% are observed, we will perform an intention-to-treat analysis.

There are no known side effects/complications related to the techniques applied, other than possible discomfort following the intervention, and any adverse events will be monitored. All participants will be instructed to contact research personnel if they experience any adverse events at any point during the study.

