### Statistical analysis and sample size calculation

#### Calculation of the sample size

A sample size calculation was performed to estimate the number of participants needed to obtain a statistical power of 0.80 at an alpha level of 0.05. A pilot study was previously conducted to calculate the sample size (unpublished). The results of this study showed improvements in the fast-twitch muscle fibres in both groups after the intervention. In the experimental group, the mean number of fast-twitch muscle fibres was 1.2 (± 0.7), and in the control group, it was 1.1 (± 1.7). Based on these results, we used Student’s bilateral *t* test to calculate the sample size, which was a minimum of 72 participants per group. To estimate the sample loss during the study, loss percentages from 0 to 20% were assumed. For each patient that is expected to terminate their participation in the study, two new patients will be included. Thus, considering a loss of 20%, the sample size was a minimum of 86 patients in each group.

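### Intention-to-treat analysis is conditional on observed dropout above 15%, and no analysis set is named for dropout at or below that level

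*Protocol article*

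**What the plan says.** The rule stands in the Interventions section of the protocol article: "In the event that dropouts of more than 15% are observed, we will perform an intention-to-treat analysis". The Data analysis section lists the tests but names no analysis set. Nothing elsewhere commits to analysing every randomised woman in her allocated group.

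The section on calculation of the sample size shows the dropout that the authors expected: "To estimate the sample loss during the study, loss percentages from 0 to 20% were assumed". It ends with the enrolment target: "considering a loss of 20%, the sample size was a minimum of 86 patients in each group", which makes 172 in total. It also sets a replacement rule: "For each patient that is expected to terminate their participation in the study, two new patients will be included".

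Two other statements bear on the point. The Blinding section says that participants will know their group, because only one group receives palpation as treatment. The Participants section excludes women who cannot comfortably tolerate the pelvic floor muscle examination.

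**The concern.** A condition on intention to treat has a purpose only if something else is done when the condition is not met. As written, the population for the group comparison is settled by a post-randomisation quantity, the pooled dropout rate. When that rate is 15% or lower, randomised women may be dropped from the comparison.

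The threshold measures the wrong thing. Leaving women out causes bias when those who leave differ from those who stay, and differ in number or in kind between the arms. A low pooled rate does not rule this out. What is at stake is the randomised comparison of the number of effective fast contractions, the primary outcome.

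This is not a detail left to an analysis plan that is not shown. The protocol itself fixes the rule, so an analysis plan would have to follow it or contradict it.

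**Working it through.** **Inputs from the protocol article.** Trigger: dropout above 15% (Interventions). Planned loss: 0 to 20%; 72 per group before losses and 86 after; power 0.80 and two-sided alpha 0.05 (Calculation of the sample size). Total: 172 (Abstract).

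**1. The plan's own figures.** The step from 72 to 86 reproduces as 72 × 1.20 = 86.4. Dividing by the retained fraction would give 72 / 0.80 = 90. The 72 does not reproduce from the pilot figures. With a difference of 0.1 and a pooled SD of sqrt((0.7² + 1.7²) / 2) = 1.30, a two-sided test needs 2,653 per group. That is a separate matter, and this point does not rest on it.

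**2. Where the trigger lies.** 0.15 × 172 = 25.8. So 25 dropouts (25/172 = 14.5%) do not trigger intention to treat and 26 (26/172 = 15.1%) do. The planned 20% loss is 0.20 × 172 = 34.4, which would trigger it.

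**3. How likely each branch is.** Take 172 women, independent dropout and an assumed true rate p. The chance of 26 or more dropouts is:

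| Assumed true rate | Chance that the trigger is met |
|---|---|
| 10% | 2% |
| 12% | 13% |
| 15% | 52% |
| 18% | 86% |
| 20% | 96% |

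Both branches are realistic within the planned range.

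**4. What the rule permits.** All 25 women could come from one arm, 25/86 = 29% of it, without meeting the trigger. This is a limiting case, not an estimate.

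**5. Size of the bias.** In an arm with dropout fraction f, the mean over all women is (1 − f) × completer mean + f × dropout mean. The completer mean therefore exceeds it by f × gap, where gap = completer mean − dropout mean. With the same gap in both arms:

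bias in the group difference = gap × (f_experimental − f_control).

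Assumed values, each averaging 15% overall and so not above the trigger:

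| Dropout in the two arms | Gap | Bias |
|---|---|---|
| 17% v 13% | 0.5 SD | 0.04 × 0.5 = 0.02 SD |
| 20% v 10% | 0.5 SD | 0.10 × 0.5 = 0.05 SD |
| 20% v 10% | 1 SD | 0.10 × 1 = 0.10 SD |
| 25% v 5% | 1 SD | 0.20 × 1 = 0.20 SD |

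In whole women the end rows are about 14 v 11 and 21 v 4, and the results are the same after rounding: (14 − 11)/86 × 0.5 = 0.017 and (21 − 4)/86 × 1 = 0.198. The sign reverses if the control arm loses more women. If the gaps differ between arms, the bias is f_experimental × gap_experimental − f_control × gap_control, which need not be zero even when the dropout rates are equal.

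**6. A yardstick.** With 72 per group, the effect detectable with 80% power is 2.80 × sqrt(2/72) = 0.47 SD. The range above is 0.02/0.47 = 4% to 0.20/0.47 = 43% of that. The yardstick is derived here and is not a target stated in the protocol.

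**The case against.** The strongest reply is that the rule is fixed in advance, uses a dropout percentage and not a treatment effect, and does call for intention to treat at the loss the trial planned for. At a true dropout of 20% it would be triggered about 96% of the time. Where it is not triggered, fewer women are missing. This stands as far as it goes, but the plan also allows for losses down to zero, and a smaller pooled loss can still be uneven between arms.

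A reader might draw four stronger conclusions that the documents do not support.

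- *That the primary analysis is stated to be a completer or per-protocol analysis at low dropout.* The sentence does not use the word primary and names no fallback set. A set other than intention to treat is its plain implication, not its text.
- *That palpation will drive women out of the experimental arm.* The possible discomfort mentioned in the Interventions section refers to the techniques in general, in a section that covers both programmes. Women who tolerate the examination poorly are excluded at entry, and both groups are assessed by palpation. Arm-related dropout remains possible because participants are unblinded, but this mechanism is largely screened out.
- *That the bias favours the experimental arm.* Women who make little progress without palpation could equally leave the control arm. Nothing in the document settles the direction.
- *That the analysis set can be chosen after seeing the results.* The threshold is set beforehand, and the Blinding section keeps the analysts unaware of group. The fault is that the criterion is post-randomisation and pooled, not that it is discretionary.

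**Conclusion.** The rule is wrong as written and should be corrected. It guarantees intention to treat only from 26 dropouts upward. For any lower number, which lies inside the planned range, it leaves the analysis set unnamed and implies that up to 25 of 172 randomised women may be left out.

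The resulting bias cannot be estimated from the document, because neither dropout by arm nor the outcome gap is given. Under the assumed values it runs from 0.02 SD to 0.20 SD, in either direction. The upper end needs both a very uneven split and a large gap, and should not be read as an expected value.

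Two uncertainties remain. Dropout is not defined as either stopping sessions or missing the T5 assessment. The replacement rule does not say whether women who leave stay in the analysis or in the denominator of the 15%, so even the trigger is not exact.

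**What to change.** Replace the conditional sentence in the Interventions section with:

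> The primary analysis includes all randomised women in the group to which they were allocated, whatever the dropout rate. Missing T5 outcomes are handled by a method fixed before unblinding (for example, multiple imputation using group and baseline value). Any completer or per-protocol analysis is a sensitivity analysis.

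Multiple imputation is one acceptable choice, and its details can sit in the analysis plan. What matters is that the population is unconditional and the method is settled before unblinding.

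Where it is still feasible, ask women who stop attending sessions to come to the existing T5 assessment. The Trial status section reports 165 of 172 women recruited, so for most earlier dropouts that time has probably passed.

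The cost is one sentence and a small amount of extra analysis work. The sample size does not change.

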#### Experimental group: verbal instructions + body awareness techniques + vaginal palpation

For the experimental group, the PT will provide verbal instructions to the patients about the anatomy and function of the PFMs, bladder function, and micturition; instruct them on how to perform body perception training, which includes posture and breathing movements; and instruct them on how to perform PFM contractions by using vaginal palpation as part of the treatment.

The treatment programme is based on motor learning concepts related to the PFMs [7, 15]. The steps of learning the proper muscle contractions will be grouped into the following four phases: (1) the understanding phase, as patients need to understand where the PFMs are located and how they work (cognitive function); (2) the searching phase (“Where is my pelvic floor?”), as patients need time to apply this understanding to their bodies and find where the PFMs are located, though they often need the PT to confirm the location; (3) the learning phase, as patients need to learn how to perform PFM contractions correctly after they find the PFMs, and feedback from the PT is mandatory at this point; and (4) the control phase, as most subjects will still need to work towards performing controlled and coordinated contractions, recruiting as many motor units as possible during each contraction, after having learned to contract the PFMs properly [7]. The awareness programme will last for 4 weeks and will include four outpatient consultations lasting 60 min each (1 session per week).

#### Control group: verbal instructions + body awareness techniques

For the control group, the PT will provide verbal instructions to the patients about the anatomy and function of the PFMs, bladder function, and micturition; instruct them on how to perform body perception training, which includes posture and breathing movements; and instruct them on how to perform PFM contractions without vaginal palpation during the treatment. After the end of the 4-week period, the patients will undergo the same protocol as the experimental group.

After the awareness phase with the protocol including vaginal palpation, the patients in both groups will continue PFMT for SUI management.

### Standardization of treatment

The PT who will be delivering the interventions is extensively trained in administering the standardized treatment protocols and rigorous procedures used for both the experimental and control groups. Routinely, during the course of the study, the PT will meet with the study team to ensure consistency in the protocol and to discuss any concerns that may arise.

### Primary and secondary outcome measures and assessment points

The patients will be evaluated at baseline (*week 0*) and at 4 weeks post-intervention (*week T5*) (Table 1). The study population will be characterized based on sociodemographic [age, body mass index (BMI), duration of symptoms, number of pregnancies, number of vaginal deliveries, hormone therapy (HT), ethnicity, and educational level] and clinical (PFM function and self-perceptions of the effectiveness of the perineal exercises) variables.

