## Results

The data for this trial is currently being collected, and the trial is registered at ClinicalTrials.gov, NCT 03325543. Enrolment is expected to continue through 2019, with long-term outcomes being assessed completely by 2020 for all subjects.

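### The time of the primary assessment is stated inconsistently, and the text does not place it before control participants start the palpation protocol

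*Protocol article*

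**What the plan says.** All references are to the protocol article.

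- **Objectives and hypothesis.** The primary outcome is the count of effective fast contractions, "out of ten contractions performed [11], before and immediately after the intervention". The same timing is attached to each of the other objectives, and the hypothesis concerns the state of the two groups once the interventions have been undergone.
- **Primary and secondary outcome measures and assessment points.** There are two assessments: at baseline, labelled week 0, "and at 4 weeks post-intervention", labelled week T5, with a reference to Table 1. The paragraph that defines the primary outcome gives no time of its own.
- **Interventions and Research site.** "The training programme will last for 4 weeks and will include 4 personal physiotherapy consultations", delivered as "one training session per week for 1 month (four sessions").
- **Control group.** "After the end of the 4-week period, the patients will undergo the same protocol as the experimental group". Both groups then go on with pelvic floor muscle training.
- **Results.** A status sentence refers to follow-up "with long-term outcomes being assessed completely by 2020 for all subjects", although no visit after T5 is listed in the text.

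**The concern.** The time of the primary assessment decides which treatment contrast the trial estimates. Directly after the fourth session, one arm has had palpation and the other has not, which is the contrast in the hypothesis. Once controls have begun the palpation protocol, the arms differ in when palpation was given and in what followed it.

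The text gives two descriptions of this time that do not agree, and one of them falls after the point at which controls may change protocol. A visit scheduled by the literal wording would mix the two contrasts. Dilution would push the estimate towards no difference, so a null result could not be read as evidence that palpation adds nothing.

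**Working it through.** The plan attaches no figure to the timing, so the check is a calendar followed by an illustration of size.

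**Calendar, counted in weeks from the first session**

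1. Four sessions at one per week fall in weeks 1, 2, 3 and 4. The randomised programme ends in week 4.
2. The wording in the Objectives section places the assessment right after session four, at the end of week 4 or in week 5.
3. The T5 label, read as week 5, agrees with step 2.
4. The literal wording of the assessment section gives 4 + 4 = week 8. Week 5 is one week after the programme, so on that reading the label and the words in the same sentence disagree.
5. Controls move to the palpation protocol after week 4. The earliest weekly session is therefore in week 5.

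**Control palpation sessions held by the assessment**

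The documents give no crossover start week, so it is varied here. With weekly sessions, the number held by week 8 is 8 − start week + 1, counting a week-8 session as held before the assessment:

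| Crossover starts in week | Sessions by week 8 | Sessions by week 5 |
|---|---|---|
| 5 | 4 | 0 or 1, depending on order |
| 6 | 3 | 0 |
| 7 | 2 | 0 |
| 8 | 1 | 0 |
| 9 or later | 0 | 0 |

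At week 8 the experimental arm would have had four palpation sessions and then up to four weeks of continued training. Controls would have had four sessions without palpation and then between none and four with it.

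**Illustration of what dilution would cost**

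The sample size section states 72 per group, power 0.80 and two-sided alpha 0.05. That 72 does not follow from the quoted pilot values. The difference is 1.2 − 1.1 = 0.1, the root-mean-square SD is √((0.7² + 1.7²)/2) = 1.3, and the formula gives 2,653 per group. That is a separate matter and carries no weight here. The 72 serves only as a reference size, from which the detectable effect is calculated back:

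- Detectable standardised effect: d = (1.960 + 0.842) × √(2/72) = 2.802 × 0.1667 = 0.467 SD.
- Two-sided power when a share f of that effect remains: Φ(2.802f − 1.960) + Φ(−2.802f − 1.960).

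| Share retained f (assumption) | Power |
|---|---|
| 100% | 80% |
| 75% | 56% |
| 50% | 29% |
| 25% | 11% |
| 0% | 5% |

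The documents give no basis for choosing a value of f.

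**The case against.** The strongest reply is that this is loose punctuation for a visit at 4 weeks, after the intervention. Four things support it: the T5 label in the same sentence, the four weekly sessions, the repeated timing in the Objectives section, and the delay of the control switch until the 4-week period is over. Table 1, which the sentence cites, may define T5. It was not available for this check, and that is not a fault of the plan.

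Much of this stands, and about week 5 is the more plausible intention. Two points remain. The sentence still gives a time that disagrees with the objectives and, if T5 is week 5, with its own label. And week 5 is also the first week in which a control could have a palpation session, while the text does not say which comes first.

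A reader might infer that the contrast disappears at week 8, or that only timing is left. The documents do not support that. The loss depends on the literal reading and on an early crossover, for which no start date is given. The experimental arm would also have moved on to continued training, so some difference could remain.

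A reader might also conclude that every control value obtained after crossover should be set to missing. That would remove outcomes from one arm only and, if the literal timing had been followed, possibly most of that arm's primary data.

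The mention of long-term outcomes is a status remark. It defines no endpoint and claims no randomised comparison, so it calls for an editorial change only.

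**Conclusion.** The inconsistency is certain, because both statements are in the current text. Its consequence is conditional. If assessments took place at about week 5 and before any control palpation session, the randomised contrast is intact and only the wording is wrong. If they took place at about week 8, the primary comparison is early versus delayed palpation, with up to four palpation sessions already given to controls, and the effect is probably diluted. The power figures of 56%, 29% and 11% show how quickly sensitivity falls if 75%, 50% or 25% of the effect remains. They rest on assumed shares and on an effect calculated back from 72 per group, and they are not predictions for this trial.

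The point should be settled before analysis, because it fixes what the primary result means. It does not show that the design must change.

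**What to change.** - Reconcile the Objectives, Control group and assessment-points sections. Replace the literal post-intervention wording with one time counted from the first session, set after the fourth session and with a stated window, and define T5 as that time.
- State that the T5 assessment is completed before any control participant's first palpation session.
- Check the recorded dates of T5 assessments against the dates of first control palpation sessions. Report how many control assessments, if any, came after crossover, and examine their influence in a sensitivity analysis. Do not set them to missing automatically.
- Describe any later data as follow-up without a randomised comparison of palpation with no palpation, or drop the reference to long-term outcomes.

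The cost is wording and a date check, with no new visit. The Trial status section reports 165 of 172 recruited, so most dates should already be on file. If the check finds that assessments were made late, the wording cannot restore the contrast. The report would then have to say which comparison was made.
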